#### Power analysis

We estimate a total sample size of 74 participants recruited and randomized, with 60 study completers, taking into account a likely 20% attrition rate (loss to follow-up, not tolerating the intervention) based on our previous experience with RCTs (23–25). In this study, 74 participants will be randomized to either the treatment group or control group, with each having *n* = 37. On repeated measures ANOVA, 60 study completers will allow us to observe an effect size of 0.34 at two-tailed alpha = 0.05 and Power (1-Beta) = 0.8 (cite G^*^Power software). As this is a pilot study, results will be used for power calculations in order to assess an appropriate sample size for a future larger confirmatory RCT.

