### Outcomes

All primary, secondary, and exploratory data will be collected at baseline and 8-weeks (primary study endpoint). The total time required to complete each time point assessment is 30–40 min.

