#### Exploratory outcomes

Anxiety and quality of life, as measured by Generalized Anxiety Disorder-7 (GAD-7) (21), EQ-5D-5L (22), respectively. We will also look for indications of a reduction in acute healthcare utilization (number of hospitalizations and emergency room visits) at 8 weeks post-intervention. Moreover, participant experiences and acceptability with the robot will be measured using qualitative methods (semi-structured interviews). We will also note whether feasibility outcomes have been met, wherein a) >50% of eligible participants will consent, b) recruitment goals are met during the study period (*n* = 74), and c) rate of attrition is <20% (dichotomous “yes/no”).

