### Statistical analyses

Descriptive statistics will be run with continuous variables summarized using means and standard deviations, and categorical variables summarized using counts and proportions. Primary analyses for all quantitative outcomes including the primary, secondary and exploratory outcome measures (e.g., UCLA loneliness score, PHQ-9 score, GAD-7 score) will be compared between intervention and control groups, controlling for baseline scores using linear mixed models (SAS Institute, Cary, NC). For qualitative data, thematic analysis will identify and code central themes, using NVivo software (ver.10).

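### The single attrition criterion mixes robot intolerance with loss to follow-up and names no arm, so feasibility can be declared met while more than a third of the robot arm is lost

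*Protocol article*

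**What the plan says.** All of this is in the protocol article.

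- **Power analysis.** The sample size is set out as "We estimate a total sample size of 74 participants recruited and randomized, with 60 study completers", and the gap is explained by "taking into account a likely 20% attrition rate (loss to follow-up, not tolerating the intervention"). Two different events share one allowance: having no outcome data, and not tolerating the intervention. Allocation is 37 per arm.
- **Treatment as usual.** The control group does not receive the robot. Its activities are the homes' routine care.
- **Exploratory outcomes.** Three feasibility checks are listed: consent above 50% of those eligible, recruitment of 74, and "rate of attrition is <20" per cent, judged yes or no. No arm is named. Acceptability is studied by interview, with no threshold.
- **Outcomes.** "All primary, secondary, and exploratory data will be collected at baseline and 8-weeks (primary study endpoint"); there is no visit in between.
- **Statistical analyses.** Outcomes "will be compared between intervention and control groups, controlling for baseline scores using linear mixed models". No analysis set is named.

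**The concern.** Only one arm is given a study intervention, so the intolerance part of attrition can arise only there. The control label (active control) does not change this, because usual care is what those residents already have. The consent and recruitment checks say nothing about the robot once sessions have begun. The attrition rule is therefore the only numerical feasibility criterion that poor tolerance of the robot can move, and an overall rate dilutes it with a control arm that cannot contribute such losses.

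The article says that the pilot will be used to size and inform a larger confirmatory trial. A yes that is compatible with heavy loss from the robot arm is a weak basis for that step. The efficacy comparison is also exposed, conditionally: if stopping the robot means no week-8 score, residents whom the robot suits least go missing from one arm only.

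**Working it through.** **1. The plan's own figures.** Inputs from Power analysis: 74 randomised, 60 completers, 20% attrition, effect size 0.34, two-tailed alpha 0.05, power 0.80.

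- Inflation for attrition: 60 / (1 − 0.20) = 75, against the stated 74. Conversely, 74 × 0.80 = 59.2. The figures agree to within one participant.
- Implied loss: 74 − 60 = 14, and 14/74 = 18.9%.
- Power: take 0.34 as Cohen's f for the between-groups effect in a two-measurement repeated measures ANOVA, with noncentrality f² × N × 2 / (1 + ρ) and N = 60. The detectable f at 80% power is 0.339 if ρ = 0.7, and runs from 0.26 to 0.37 as ρ goes from 0 to 1. The article does not give ρ. The stated figure can be reproduced and is not in dispute here.

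**2. What the limit allows when pooled.** 14/74 = 18.9% passes and 15/74 = 20.3% fails, so at most 14 losses are accepted. Splits that return a yes:

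| Robot losses (of 37) | Control losses (of 37) | Robot arm | Control arm | Pooled |
|---|---|---|---|---|
| 14 | 0 | 37.8% | 0% | 18.9% |
| 13 | 1 | 35.1% | 2.7% | 18.9% |
| 12 | 2 | 32.4% | 5.4% | 18.9% |
| 10 | 4 | 27.0% | 10.8% | 18.9% |

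The same limit applied to the robot arm alone accepts at most 7 of 37 (18.9%; 8/37 = 21.6% fails).

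**3. Probability of a yes.** The article gives no arm-specific rates, so those below are assumptions. Losses are binomial with 37 per arm. The pooled rule passes if the two counts sum to 14 or fewer, the robot-arm rule if the robot count is 7 or fewer.

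| True rate, robot | True rate, control | Pooled rule passes | Robot-arm rule passes |
|---|---|---|---|
| 25% | 5% | 0.87 | 0.26 |
| 30% | 5% | 0.70 | 0.09 |
| 30% | 10% | 0.47 | 0.09 |
| 20% | 20% | 0.48 | 0.53 |

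**4. Margin.** The last row is the planning assumption taken literally: P(X ≤ 14), with X binomial (74, 0.20), is 0.477. The planned loss of 14 is also the largest count that passes, and one further loss turns yes into no.

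**5. Conditional effect on the efficacy comparison.** With assessments only at baseline and week 8, and baseline used for adjustment, a resident with no week-8 score adds little or nothing to the treatment contrast. Suppose a share p of the robot arm is intolerant and unassessed, and would have scored δ standard deviations worse at week 8 than the rest of that arm, after baseline adjustment. The robot mean is then too favourable by p × δ. Assumed values, none from the article: p = 0.15 and δ = 0.5 to 1.0, giving 0.15 × 0.5 = 0.075 and 0.15 × 1.0 = 0.15 SD. With 30 per arm and an assumed baseline correlation of 0.5, the standard error is √[(1 − 0.25) × 2/30] = 0.224 SD, and a nominal 5% test would reject about 6% to 10% of the time under no effect.

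**The case against.** **A reader might infer that the plan removes robot failures from the efficacy analysis.** The documents do not support this. The 60 completers are a sample-size assumption. The Statistical analyses section names no completer or per-protocol set, and the Outcomes section makes no exception to week-8 assessment for residents who stop sessions. Analysis sets and missing-data rules may sit in a full protocol or SAP that is not shown, and their absence from an article is no finding. The bias in step 5 is therefore a scenario. It needs intolerant residents to be unassessed at week 8, and a deficit that baseline adjustment does not remove.

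**A reader might also infer that the plan's expected attrition fails its own criterion.** Taken literally, 20% is not below 20%. On the plan's own counts, however, the loss is 14 of 74, or 18.9%, which passes. The 20% reads as a rounded allowance. What stands is the lack of margin.

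**On the feasibility rule,** it is fair to say that pooled is an interpretation, that a split such as 13 against 1 is extreme, that the criterion is exploratory and one of three, that interviews cover acceptability, and that nothing stops the authors from reporting attrition by arm. Pooled is still the natural reading, since no arm is named and the 20% allowance is applied to all 74. Less extreme rates (25% and 5%) give a yes with probability 0.87. The interviews have no threshold, so they cannot correct the yes/no verdict.

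**Conclusion.** The point holds for the feasibility criterion. The article itself states both the merged definition and the limit, so this part does not depend on material left to another document. Read as pooled, the rule can return a yes with up to 37.8% of the robot arm lost. At assumed true rates of 30% and 5%, it does so with probability 0.70, against 0.09 for the same limit in the robot arm. It also has no margin at the planned loss, with a pass probability of 0.48 if true attrition is 20%. The counts are exact; the probabilities rest on the assumed rates and independent binomial losses.

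For efficacy, only a conditional risk stands: if those who stop the robot are handled as non-completers, as the power section's arithmetic treats them, and have no week-8 score, the loss is one-sided and could favour the robot. Its size depends wholly on assumed inputs. The matter should be corrected because the pilot is meant to inform a larger trial, but the sample size is not in error on this account.

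**What to change.** 1. Define attrition as having no week-8 UCLA 20-item score.
2. Count robot-session discontinuation separately and report it as its own result for the robot arm.
3. State that residents who stop sessions are still assessed at week 8, if they agree, and are analysed in the arm to which they were assigned.
4. Judge the attrition criterion in the robot arm as well as overall, each with a 95% confidence interval, and say how the limit relates to the planning rate so that the lack of margin is deliberate or removed.

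The cost is mainly wording. The week-8 assessment is already planned, at 30 to 40 minutes per resident. With only 37 residents, the robot-arm verdict will be imprecise (it passes with probability 0.53 when that arm's true rate is 20%), so the interval should be read with the yes or no. The feasibility verdict and the effect estimate may both turn out slightly less favourable to the robot.

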#### Subgroup analyses

##### Sex-based subgroup analysis

We will complete a subgroup analysis reporting main outcomes in men and women, respectively. Sex, along with other baseline characteristics, will also be included as covariates in statistical models to capture their effects on outcomes. We will conduct subgroup analyses on primary outcome in patients stratified by site.

## Discussion

The proposed study is the first RCT investigating the effects of a humanoid robot intervention on mental health outcomes in older adults. Low staff-to-resident ratios as well as funding shortages and social distancing restrictions in LTC homes have underscored the urgent need for effective, acceptable, and feasible interventions to address loneliness in this setting. Artificial Intelligence (AI)-based humanoid robots, such as the Grace robot, can provide the complex interactions required for human-like social interaction, can foster connections, and engage participants to promote positive health outcomes (26, 27). Humanoid robots may also decrease barriers to social interaction in LTC homes, such as limited mobility and poor health. This is especially relevant during COVID-19 and any infectious-disease or immunocompromised case, as participants can experience social interaction without increasing their risk of infection (28). The proposed study investigating the effect of a humanoid robot interaction intervention vs. TAU on loneliness and mental health outcomes will be the first of its kind in Canada. If successful, this study will pave the way for humanoid robots as a novel approach to promote aging in place, which is likely to become increasingly cost-effective in the coming years. Furthermore, humanoid robots have the potential to become an accessible and scalable alternative to loneliness interventions in LTC settings. A recent report from the Stanford Institute for Human-Centered Artificial intelligence determined that costs of robots are steadily decreasing as AI investments continue to climb worldwide and AI capabilities improve (29).

The potential benefits of the proposed pilot include decreased loneliness, anxiety, depression, and other improved mental health outcomes in older adults, as well as decreased healthcare utilization and improved overall quality of life. The results from this cutting-edge study will provide pilot data to inform a larger three-arm, multi-site confirmatory RCT assessing the effects of the Grace robot on mental health outcomes of older adults in LTC homes.

## Ethics statement

Ethical approval was not provided for this study on human participants because Research Ethics Board Approval has not yet been requested but will be sought at the following sites: CIUSSS-Center-Ouest-de-l'Ile; CIUSSS-Ouest-de-l'Ile in Montréal, QC. Informed consent will be obtained from all study participants by trained research staff at all sites in accordance with these sites' respective governing ethics boards' guidelines. Written informed consent was not provided because recruitment has not yet started. Written informed consent will be requested from all participants.
